## Abstract

**Background:**

Integrating behavioral health services into pediatric primary care can improve access to care, especially for children marginalized by poverty and racial/ethnic minority status. In primary care, a common presenting concern is attention-deficit/hyperactivity disorder (ADHD). Services in primary care for marginalized children with ADHD typically include medication alone; therapy to improve skills and build relationships is less available. This study evaluates the effectiveness of a behavioral intervention offered through primary care for marginalized families coping with ADHD (Partnering to Achieve School Success, PASS) compared to treatment as usual (TAU).

**Method:**

Three hundred participants will be randomly assigned to PASS or TAU. Participants include children ages 5 to 11 who have ADHD and are from economically marginalized families. PASS is a personalized, enhanced behavioral intervention that includes evidence-based behavior therapy strategies and enhancements to promote family engagement, increase caregiver distress tolerance, and provide team-based care to improve academic and behavioral functioning. TAU includes services offered by primary care providers and referral for integrated behavioral health or community mental health services. Outcomes will be assessed at mid-treatment (8 weeks after baseline), post-treatment (16 weeks), and follow-up (32 weeks) using parent- and teacher-report measures of service use, child academic, behavioral, and social functioning, parenting practices, family empowerment, and team-based care. Mixed effects models will examine between-group differences at post-treatment and follow-up. Analyses will examine the mediating role of parenting practices, family empowerment, and team-based care. Subgroup analyses will examine differential effects of intervention by child clinical characteristics and socioeconomic factors.

**Discussion:**

This study is unique in targeting a population of children with ADHD marginalized by low socioeconomic resources and examining an intervention designed to address the challenges of families coping with chronic stress related to poverty.

**Trial registration:**

This study was registered on clinicaltrials.gov (NCT04082234) on September 5, 2019, prior to enrollment of the first participant. The current version of the protocol and IRB approval date is October 4, 2023. Results will be submitted to ClinicalTrials.gov no later than 30 days prior to the due date for the submission of the draft of the final research report to the Patient-Centered Outcomes Research Institute.

**Supplementary Information:**

The online version contains supplementary material available at 10.1186/s12875-024-02473-7.

## Background and rationale

Behavioral health conditions are estimated to occur among at least 20% of children and adolescents [1], but only about one in five children with significant mental health needs receive evidence-based services [2]. Disparities in service access and use are substantial; children marginalized by low family income who disproportionately belong to underrepresented racial/ethnic groups utilize mental health services significantly less than those who are more advantaged [3, 4].

Children from economically marginalized groups face numerous challenges that contribute to poorer health outcomes [5]. Poverty confers upon these children enormous risk, including chronic stress related to single parenting, frequent life transitions, parental psychopathology, and exposure to violence. These factors, in turn, are associated with disrupted parent–child attachments, negative parenting, and increased risk of comorbid child mental health conditions [6, 7]. Further, these children often attend schools that are under-resourced and stressed by staff shortages, high rates of staff turnover, and the challenge of supporting students living in poverty [8].

Lack of service use is a significant problem because untreated mental health conditions are associated with poor outcomes [9]. Pediatric primary care has become a major venue for the delivery of behavioral health services, in response to the urgent need to improve access to care and reduce disparities in service utilization. Behavioral health services in primary care target a broad range of conditions, including ADHD, given its high prevalence (estimated 9%) [10] and associated impairments [11]. In fact, up to 25% of referrals to integrated behavioral health in primary care providers are for concerns related to attention and school problems [12]. Children with ADHD are at risk for numerous adverse outcomes later in adolescence, including anti-social behavior and incarceration, school disengagement and drop out, [13–15] and more frequent medical visits [16]. Families of children with ADHD spend more money per year on health care for their children than families of children without the disorder [17]. In addition, relative to a typically developing child, the incremental cost to educate a child with behavior disorders is substantially higher largely due to costs associated with special education placement, grade retention, and disciplinary incidents [18]. In response to the enormous need of children with ADHD and ongoing problems with access to services, the American Academy of Pediatrics (AAP) has highlighted primary care as a major venue for assessment and management of this condition [19].

This study has a broad focus on the management of behavioral health conditions in primary care. ADHD is used as an exemplar [20] because of the feasibility of managing this disorder in primary care. This study addresses a high priority identified by the Institute of Medicine to compare the effectiveness of interventions based in primary care for children with ADHD [9].

The optimal strategy for improving outcomes for most children with ADHD includes behavior therapy in combination with medication [21–23]. Despite current medication shortages, medication may be easier to obtain through primary care than behavioral interventions, and the majority of children with ADHD (62%) receive medication [10]. In contrast, behavior therapy is less accessible; about 8% of families reported they currently receive this intervention and only 31% have ever received this service [10]. As a result, families of children with ADHD, particularly those who are economically marginalized, may have access to only one mode of treatment (medication), which may address symptoms but not critical areas of impairment and may not be acceptable or preferred by families [24].

Providing services in primary care can improve access [25] to behavioral health care. Although studies have generally demonstrated the effectiveness of behavioral interventions provided in primary care [26], research on the effectiveness of behavior therapy provided in primary care for marginalized children with ADHD is very limited. The studies conducted to date have not focused specifically on children with ADHD [27–29]; do not include enhancements tailored to economically marginalized families [27, 29]; and/or are too brief to include some critical components of evidence-based behavior therapy [28].

This study addresses a priority for comparative effectiveness research, listed in the first quartile by the Institute of Medicine: Examine the effectiveness of treatment strategies based in primary care for ADHD in children [9]. In this study, we will compare the effectiveness of enhanced behavior therapy offered in primary care, known as Partnering to Achieve School Success (PASS), to treatment as usual (TAU) informed by AAP guidelines for ADHD and facilitated by electronic practice supports as well as access to behavioral health services that are integrated into primary care practice. Enhancements to behavior therapy include strategies to integrate medical and behavioral health care, promote family motivation and engagement, support family-school-primary care collaboration, and support families in coping with chronic stress. Of note, PASS also includes the involvement of a Community Health Partner or patient navigator; research has shown that these individuals can be effective in improving patient engagement in behavioral health services [30]. The study is designed to examine the effectiveness of PASS in improving service use and outcomes important to families of children with this disorder, specifically academic performance, behavioral compliance, and interpersonal relationships.

### Study objectives

The study has four objectives. The first objective is to evaluate differences between PASS and TAU in improving utilization of ADHD services and patient-centered outcomes for children with ADHD from economically marginalized families at post-treatment (16 weeks after baseline) and follow-up (32 weeks after baseline). We hypothesized that, compared to TAU, families in PASS will show greater use of services for ADHD, and children in PASS will demonstrate greater improvements in academic performance, behavior compliance, interpersonal competence, life satisfaction, and ADHD symptoms.

Second, we will compare PASS and TAU on parenting practices, caregiver sense of empowerment to navigate systems of care, and caregiver perceptions of the quality of team-based care. It is hypothesized that, compared to TAU, families in PASS will show a greater reduction in negative parenting practices, an improvement in their sense of empowerment in being able to navigate care delivery systems, and an increase in their perceptions of team-based care. Third, we will explore whether changes in caregiver processes (parenting practices, caregiver sense of empowerment, perceptions of team-based care) mediate the effect of intervention on child outcomes. Finally, we will explore the heterogeneity of treatment effect for families of varying levels of socioeconomic resources, caregivers with varying levels of stress and health literacy, medicated versus unmedicated children, and children with varying levels of mental health symptom severity at baseline.

### Trial design

The study is a two-group, parallel randomized controlled trial**.** Patients will be randomly assigned to PASS or TAU, 150 participants per condition. Randomization will be stratified by practice (seven practices) and parental report of ADHD medication usage (yes, no) at time of random assignment. We will request that parents in PASS and TAU report about services they are receiving in the community during the intervention and follow-up periods. Outcome measures pertaining to Objectives 1 and 2 will be administered at baseline, post-treatment (16 weeks after baseline), and follow-up (32 weeks after baseline) from caregivers and teachers. Caregivers, but not teachers, will also be asked to complete a brief set of outcome measures at a mid-treatment time point (8 weeks after baseline). During the follow-up period, families in PASS will no longer receive the PASS intervention, and families in both conditions will have access to behavioral health services integrated into primary care. Family attendance at sessions and adherence to recommended treatment strategies will be assessed continuously during the intervention. Family utilization of behavioral health services in primary care prior to the study, during the intervention period, and during follow up will be monitored to examine the contrast in service delivery between treatment conditions. Subgroups identified by level of socioeconomic resources, caregiver stress, and caregiver health literacy, child clinical characteristics, as well as child medication status at baseline will be delineated to examine whether there are differences in outcome as a function of subgroup. PASS will be provided in the context of the integrated primary care program at our institution. Integrated primary care providers will incorporate PASS sessions into their clinical schedules, deliver PASS to families, and bill for services as they typically do in practice. To promote participant retention in the study, newsletters will be disseminated to caregiver participants on a regular basis.

### Conceptual framework

The conceptual framework (Fig. 1) for the treatment comparison (PASS vs. TAU) is based upon evidence that integrating enhanced behavior therapy services into primary care improves patient-centered outcomes and increases service utilization [27]. The PASS intervention includes evidence-based behavior therapy (specifically behavioral parent training) and enhancements to promote family engagement in the intervention, caregiver ability to cope with chronic stress related to parenting and life circumstances (distress tolerance), caregiver motivation for change, family-school collaboration, and family involvement in team-based health care. Consistent with a developmental-ecological framework [31], PASS is designed to align systems of care (family, school, primary care) to promote healthy child development. PASS is based on a team-based medical and behavioral health service model that includes regular collaboration between the PASS clinician and the primary care provider (PCP). To assist families in overcoming barriers to care, sustaining their engagement in PASS, and obtaining needed community resources, PASS includes support from a Community Health Partner (described below).

**Fig. 1 Fig1:**
[figure not shown]
Conceptual Model for PASS intervention

According to self-determination theory [32], engagement and motivation for change are fostered by supporting caregivers’ autonomy, competence, and relatedness. PASS includes strategies to encourage caregivers’ autonomy, competence, and relatedness so that they are empowered to effectively navigate systems of care. In addition, PASS clinicians support caregiver autonomy by encouraging active involvement in team-based care that is tailored to family goals and preferences for treatment. Further, to promote caregivers’ sense of competence, PASS clinicians support consistent implementation of recommended evidence-based strategies (e.g., effective parenting practices), and partner with families to address barriers to implementation.

We propose that several factors, including family socioeconomic resources, caregiver stress and support, caregiver health literacy, and child medication status, will contribute to changes in service utilization and critical care processes (parenting effectiveness, caregiver empowerment, caregiver perceptions of team-based care, and level of family-school collaboration). In turn, we propose that changes in these proximal variables will lead to improved patient-centered outcomes (behavior compliance, homework performance, academic achievement, child life satisfaction, interpersonal relationships, and ADHD symptoms) [26, 33].

## Method

### Participants, interventions, and outcomes

#### Study setting

The study will be conducted in seven practices in the primary care network affiliated with a large children’s hospital in the Northeastern United States. These practices were chosen because they serve a relatively high percentage of economically marginalized families who disproportionately belong to underrepresented racial and ethnic groups (mostly Black/African American). See Table 1 for demographic information about each of these practices.

**Table 1 Tab1:** Demographic characteristics of the targeted primary care practices

Study Site	% Medicaid	% Black/African American	% White	% Hispanic
Site A	93%	93%	2%	4%
Site B	92%	89%	4%	6%
Site C	89%	58%	26%	11%
Site D	39%	19%	69%	7%
Site E	60%	29%	61%	4%
Site F	36%	46%	35%	14%
Site G	60%	32%	36%	23%

#### Eligibility criteria

Participants will include children 5 to 11 years of age who are diagnosed with ADHD, and their parents/caregivers. The following are the inclusion criteria:Child has an existing diagnosis of ADHD, as indicated in the electronic health record (EHR), and exhibits evidence of current impairment, as indicated by the parent.Child is 5 to 11 years of age at time of referral.Child has at least one parent or legal guardian who speaks English or Spanish.Child appears to live in an economically marginalized family, as indicated by eligibility for Medicaid or Children’s Health Insurance Program in Pennsylvania or child living in a census tract or census block with median income at or below two times the federal poverty level (child’s home address extracted from EHR).

The following are the exclusion criteria:Child has autism spectrum disorder and/or an intellectual disability, as reported by the referring clinician or parent, and/or indicated in the EHR.Child has a comorbid condition (e.g., depression, traumatic stress) that is a major clinical concern and requires an alternative form of treatment, as reported by the parent during an initial phone interview. As a rule, children with comorbid conditions will be included.Child is receiving psychological therapy from another provider at the time of recruitment.Child has a sibling currently involved in the intervention or follow-up period of the study at the same time.Child has received services from the integrated behavioral health team within the last 6 months (these children are considered “actively involved in care” and will be referred back to the provider of record).

#### Intervention conditions

The comparators in this study are enhanced behavior therapy (PASS) and TAU informed by AAP guidelines for ADHD [19] and facilitated by electronic practice supports, including access to integrated behavioral health services offered in the practice.

#### Partnering to Achieve School Success (PASS)

PASS is a personalized, enhanced behavioral intervention for ADHD that includes evidence-based behavior therapy strategies and enhancements to promote family engagement in treatment, increase caregiver distress tolerance [34], and improve team-based care [35]. PASS was designed based on feedback from families, behavioral health clinicians, caregivers, and educators for use with families of children with ADHD in the context of primary care practices serving primarily economically marginalized families. PASS is designed to modify contexts of development (family and school) and align systems of care (family, school, primary care) to prevent unhealthy patterns of behavior. This intervention includes regular collaboration between the PASS clinician and PCP.

PASS therapists utilize *engagement and motivation* strategies during each session to reinforce help-seeking behavior, support family empowerment, and encourage family adherence to recommended strategies. *Team-based care* has been incorporated based on feedback from our community partners and focuses on: (a) regular communication between the PASS provider and PCP and (b) the development of a problem-solving partnership between caregivers and teachers to address school problems. PASS content is delivered in a modular format based on family goals (e.g., focus on school performance vs. home behavior vs. peer relationships) as delineated in the family-centered treatment plan developed in partnership with the family and PCP. (See additional file 1 for an outline of PASS with details about core principles and intervention modules.) In addition, PASS includes the involvement of a Community Health Partner [35], a bachelor’s level staff member who contacts families by phone on an ongoing basis to: (a) promote attendance and implementation of PASS strategies, (b) assist in resolving barriers to treatment, and (c) guide families to community resources as needed. Community health partners have been shown repeatedly to be helpful in promoting engagement in services and improving the cultural effectiveness of care [30, 36].

#### Treatment as usual (TAU)

The control condition (TAU) includes access to existing integrated behavioral health service in primary care. Services provided to families in primary care during the 16-week intervention period are highly variable. The lag time from referral to first appointment and the availability of follow-up appointments after first visit vary markedly across practices. TAU does not include support from a Community Health Partner. Both conditions will include ongoing pediatric health care informed by AAP guidelines for managing ADHD [19] and facilitated by electronic practice supports, which have been successfully incorporated into the EHR to guide PCPs in implementing ADHD guidelines. Families assigned to TAU may be referred for community-based behavioral health services during the study period.

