### Sample size

Based on prior research [26, 28, 35], the magnitude of the effect size reflecting the degree of change in response to PASS vs TAU for service use and child outcomes (Objective 1) and care processes (Objective 2) is expected to be the 0.35 to 0.60 SD range. Based on prior research using a similar behavioral intervention [41], we assumed a standard deviation for a single observation = 0.50 and an autocorrelation = 0.3. Projecting an enrollment of 300 participants (150 per condition), and given an expected 20% attrition rate, we expect 240 participants will provide parent-report and child self-report data at baseline and at least one other data collection point. Using statistical methods described below, analytic models will achieve 85% power to detect an effect size as small as 0.30 SD. Given the challenges of collecting data from teachers related to the COVID-19 pandemic, the number of evaluable cases will be well below 240 (estimated to be 100). As such, analyses of teacher-report data will be exploratory. In addition, analyses of mediation (Objective 3) and subgroup effects (Objective 4) will be exploratory.

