## A priori plans for data analysis for each objective

### Objective 1 (Evaluate differences between PASS and TAU in improving service utilization and child health outcomes)

To evaluate changes in service utilization, we will examine between-group changes in the proportion of children receiving mental health services (i.e., outpatient mental health therapy, school mental health services and special education services, and psychotropic medication) from pre-treatment to post-treatment to follow-up using the McNemar test. To evaluate the effect of intervention on child outcomes, a mixed effects model with repeated measures (MMRM) will be the general analytical approach employed. The model will examine intervention effects across four time points (baseline, mid-treatment [parent report of homework performance and behavior compliance only], post-treatment, follow-up). Data for all participants randomized to treatment condition will be included in the analytic model, consistent with an intent-to-treat (ITT) approach. Mixed effects models will estimate within-subject effects by time and between-treatment effects, as well as the interaction of time by treatment. A significant time by treatment interaction will indicate that one treatment is superior to the other. MMRM will include the fixed categorical effects of treatment, time, randomization stratification factor (medication status and primary care practice), and treatment-by-time interaction as well as covariates as indicated. Within-participant error variance–covariance will be assumed to be an unstructured matrix. Point estimates and confidence intervals for the mean change in outcomes for each treatment group as well as the difference in the estimated mean change between groups will be calculated.

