#### Objective 4 (Examining Heterogeneity of Treatment Effects; HTE)

Our general strategy is to determine whether the effect of treatment on outcomes varies as a function of baseline level of family resources, caregiver health literacy and stress, child medication status, and child mental health symptom severity at baseline, following the recommendations of Wang and Ware [65]. We will use a regression modeling approach with the outcome being change from baseline to post-treatment/follow-up, treatment groups being the independent variable, a subgrouping variable or covariate being the moderator tested, and the test of moderation being the interaction of treatment by the covariate. A significant interaction term indicates that treatment varies as a function of subgroup. For a subgroup variable with more than two levels (e.g., caregiver stress), the presence of a significant treatment by subgroup variable interaction will be followed by a series of post hoc analyses to conduct pairwise group comparisons. The *p* values for post hoc analyses will be used to calculate Bonferroni adjusted *p* values and false discovery rates (FDR) resulting from multiple comparisons [66, 67]. Given that HTE analyses will likely be underpowered, a consideration of Bonferroni adjusted values and FDR in the discussion of the heterogeneity of treatment effects will be informative.

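### Objective 4 tests socioeconomic moderation with no practice term, although the comparator varies by practice, so an apparent socioeconomic difference may partly reflect practice differences in TAU supply

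*Protocol article*

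**What the plan says.** All references are to the protocol article.

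- **Treatment as usual (TAU):** services during the 16 weeks are described as highly variable. "The lag time from referral to first appointment and the availability of follow-up appointments after first visit vary markedly across practices".
- **Study setting, Table 1** ("Demographic characteristics of the targeted primary care practices"): Medicaid shares are 93%, 92% and 89% at Sites A to C, and 39%, 60%, 36% and 60% at Sites D to G.
- **Trial design and Assignment of interventions:** randomisation is 1:1, stratified by practice (seven) and ADHD medication status.
- **Objective 1 analysis:** "MMRM will include the fixed categorical effects of treatment, time, randomization stratification factor (medication status and primary care practice), and treatment-by-time interaction". No treatment-by-practice term is named.
- **Objective 4 analysis:** the moderators are "baseline level of family resources, caregiver health literacy and stress, child medication status, and child mental health symptom severity at baseline". The model regresses change on treatment, with "a subgrouping variable or covariate being the moderator tested, and the test of moderation being the interaction of treatment by the covariate". Practice is named neither as a covariate nor as a moderator. Medication status, the other stratification factor, is a moderator.
- **Sensitivity analyses:** GEE covers Objectives 1 and 2 and deals with correlation within aggregates. The Objective 4 sensitivity analysis concerns combined mediation and moderation. Neither lets the treatment effect differ by practice.
- **Sample size:** "analyses of mediation (Objective 3) and subgroup effects (Objective 4) will be exploratory".

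**The concern.** Stratified randomisation protects the PASS-minus-TAU contrast. It does not protect the attribution of a difference in that contrast to a family characteristic, because family resources are not randomised. If practices with scarce TAU appointments show a larger contrast, and also serve poorer families, a model without practice can credit the practice difference to family poverty.

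A practice main effect would not help, because it adjusts the outcome level in each practice and not the size of the treatment effect there. Adding the Objective 1 covariates to the Objective 4 model would therefore leave the problem in place.

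At stake is the reading of a stated objective. A finding that poorer families benefit more, and a finding that PASS adds more where usual care is scarce, call for different implementation advice. The article lists examination of differential effects by socioeconomic factors among the study's strengths.

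**Working it through.** The article gives no power or precision figure for Objective 4, so there is none to reproduce.

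**Inputs from the article.** Evaluable sample 300 × (1 − 0.20) = 240; seven practices; 1:1 allocation within practice; Table 1 Medicaid shares p = 0.93, 0.92, 0.89, 0.39, 0.60, 0.36, 0.60.

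**Assumptions, not in the article.** Equal practice sizes; a binary low-resource indicator whose prevalence follows p; outcome SD 1; no true moderation by resources; larger PASS effects at Sites A to C than at D to G.

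**Step 1: how far practice tracks poverty.** Mean p = 4.69/7 = 0.67. The between-practice variance is 0.0518 and the total is 0.67 × 0.33 = 0.2211. The between-practice share is 0.0518/0.2211 = 0.23.

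**Step 2: expected bias.** Without a treatment-by-practice term,

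bias = Cov(practice effect, p) / [0.67 × 0.33].

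Deviations of p from 0.67 sum to +0.73 over Sites A to C and −0.73 over D to G.

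- Effects −0.6 and −0.1 SD: covariance = −0.5 × 0.73/7 = −0.0521; bias = −0.0521/0.2211 = −0.24 SD.
- Effects −0.5 and −0.2 SD: covariance = −0.3 × 0.73/7 = −0.0313; bias = −0.14 SD.

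Shrinking the spread of p shrinks the bias in proportion.

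**Step 3: simulation** (4,000 trials per row, test at 0.05; SE is for the interaction).

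| Spread of p vs Table 1 | Effects A–C / D–G | Bias, planned model | False positives | SE | Bias with treatment × practice | False positives | SE |
|---|---|---|---|---|---|---|---|
| full | −0.6 / −0.1 | −0.24 | 14% | 0.28 | 0.00 | 4% | 0.325 |
| full | −0.5 / −0.2 | −0.14 | 8% | 0.28 | 0.00 | 5% | 0.325 |
| half | −0.6 / −0.1 | −0.12 | 7% | 0.28 | 0.00 | 5–6% | 0.29 |
| half | −0.5 / −0.2 | −0.06 | 5% | 0.28 | 0.01 | 5% | 0.29 |
| one third | −0.6 / −0.1 | −0.08 | 6% | 0.28 | 0.00 | 5% | 0.29 |
| one third | −0.5 / −0.2 | −0.04 | 5% | 0.28 | 0.01 | 5% | 0.29 |
| full | −0.6 / −0.1, assigned to practices at random | 0.00 | 6% | 0.28 | 0.00 | 4% | 0.325 |

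A practice main effect alone changes almost nothing: in the first row the bias is −0.25 SD with 14% false positives.

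**Step 4: a harsher corner.** With a continuous moderator, the full Table 1 between-practice share (0.234), a practice-effect SD of 0.3 and exact alignment with poverty, the bias is √0.234 × 0.3 = 0.15 SD per SD of moderator, and false positives reach 21% to 23%. Nothing in the article supports alignment that strong.

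**Step 5: cost of the remedy.** The SE ratio is 0.325/0.279 = 1.17 at the full Table 1 spread, 0.292/0.280 = 1.04 at half and 0.287/0.280 = 1.03 at one third. For a single practice, 240/7 is about 34 children, or 17 per arm, so the SE is √(2/17.1) = 0.34 SD and the 95% interval is about ±0.67 SD.

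**The case against.** Several points on the other side are sound.

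- **Alignment is assumed.** The article says TAU access varies between practices, not that it varies with Medicaid share. When the same effects are assigned to practices at random, the bias averages zero.
- **Table 1 describes practice populations.** Enrollees qualify by Medicaid or CHIP eligibility or by "child living in a census tract or census block with median income at or below two times the federal poverty level", so families in the trial will probably be more alike across practices. The planned socioeconomic measures are income, education and financial strain, not Medicaid status. At a third of the Table 1 spread, false positives are close to nominal.
- **Objective 4 is exploratory** and the article itself expects it to be underpowered.
- **The check can be run later.** Practice is recorded and service use is monitored. A full analysis plan, not shown, may already include a practice term.

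These points limit the size and the certainty. They do not remove the gap: the article writes out the Objective 4 model, says a significant interaction shows that treatment varies with the subgroup, and leaves out the one stratification factor that it says alters the comparator. Exploratory status tempers a claim but does not make a confounded interaction interpretable.

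A reader might also infer that PASS delivery differs by practice. The article does not say so: the Discussion says only that scheduling might be constrained, and the training section provides for extra clinicians so that PASS is delivered on time. The point rests on TAU variation alone.

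**Conclusion.** The point holds as a limit on interpreting Objective 4. As written, the model cannot separate family-level socioeconomic moderation from practice-level differences in TAU supply. Under effects aligned with practice poverty, the bias is about 0.04 to 0.24 SD and the false-positive rate 5% to about 14%. The upper end needs the full Table 1 spread and effects of −0.6 versus −0.1 SD, neither of which the article establishes for enrollees.

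Two stronger readings are tempting. One is that socioeconomic moderation will absorb site differences; the documents support only that it may. The other is that the main PASS-versus-TAU result is compromised. It is not: allocation is stratified by practice, and practice is in the Objective 1 model. This is a low-cost improvement to an exploratory analysis.

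**What to change.** In the Objective 4 section:

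1. For each socioeconomic moderator, pre-specify a companion sensitivity model that adds practice and treatment-by-practice terms, or that centres the moderator within practice.
2. Describe a socioeconomic difference as a family-level effect only if it persists within practices. Judge this on the estimate and its interval, not on significance alone, because the within-practice interval is wider. Otherwise report it as not separable from practice.
3. Report the treatment effect by practice descriptively, beside the service use already monitored under Trial design.

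If an analysis plan already does this, a sentence pointing to it is enough.

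The cost is wording; no new data are needed. The standard error on the exploratory interactions widens by about 3% if enrollees are alike across practices and up to about 17% at the Table 1 spread. Practice-specific estimates will be imprecise, at about ±0.67 SD, and cannot show which practices drive the overall result.
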